## Abstract

**Introduction:**

Fetal and neonatal alloimmune thrombocytopenia (FNAIT) may lead to severe fetal or neonatal bleeding and/or perinatal death. Maternal alloantibodies, targeted against fetal human platelet antigens (HPAs), can result thrombocytopenia and bleeding complications. In pregnancies with known immunisation, fetal bleeding can be prevented by weekly maternal intravenous immunoglobulin infusions. Without population-based screening, immunisation is only detected after birth of an affected infant. Affected cases that might have been prevented, when timely identified through population-based screening. Implementation is hampered by the lack of knowledge on incidence, natural history and identification of pregnancies at high risk of bleeding. We designed a study aimed to obtain this missing knowledge.

**Methods and analysis:**

The HIP (HPA-screening in pregnancy) study is a nationwide, prospective and observational cohort study aimed to assess incidence and natural history of FNAIT as well as identifying pregnancies at high risk for developing bleeding complications. For logistic reasons, we invite rhesus D-negative or rhesus c-negative pregnant women, who take part in the Dutch population-based prenatal screening programme for erythrocyte immunisation, to participate in our study. Serological HPA-1a typing is performed and a luminex-based multiplex assay will be performed for the detection of anti-HPA-1a antibodies. Results will not be communicated to patients or caregivers. Clinical data of HPA-1a negative women and an HPA-1a positive control group will be collected after birth. Samples of HPA-1a immunised pregnancies with and without signs of bleeding will be compared with identify parameters for identification of pregnancies at high risk for bleeding complications.

**Ethics and dissemination:**

Ethical approval for this study has been obtained from the Medical Ethical Committee Leiden-The Hague-Delft (P16.002). Study enrolment began in March 2017. All pregnant women have to give informed consent for testing according to the protocol. Results of the study will be disseminated through congresses and publication in relevant peer-reviewed journals.

**Trial registration number:**

NCT04067375.

Strengths and limitations of this studyThe human platelet antigen-screening in pregnancy study is a unique prospective and completely non-interventional screening study with a large cohort that enables assessing the true natural history of fetal and neonatal alloimmune thrombocytopenia (FNAIT).The unique infrastructure in the Netherlands with one national referral laboratory for FNAIT (Sanquin, Amsterdam) collaborating with the national fetal therapy centre (Leiden University Medical Centre, Leiden) will result in complete data and focus on both laboratory and clinical parameters.A limitation of the study is that we rely on the clinical judgement of bleeding tendency after birth and do not obtain cord blood platelet counts or perform routine neonatal cerebral ultrasounds. Therefore, we may still underestimate disease prevalence due to subclinical cases.

## Introduction

Fetal and neonatal alloimmune thrombocytopenia (FNAIT) is the most frequent cause of severe thrombocytopenia in term-born infants.^1 2^ FNAIT is caused by the production of maternal alloantibodies against the paternally derived, fetal human platelet antigens (HPAs). Clinical consequences can vary from an asymptomatic thrombocytopenia to minor skin haemorrhage, such as haematoma or petechiae, or ultimately severe internal organ and intracranial haemorrhage (ICH).^3 4^ Bleeding complications that, in subsequent pregnancies, can be effectively prevented by weekly administration of intravenous immunoglobulins (IVIg) to the mother.^5^ The vast majority of cases with (severe) clinical consequences are caused by maternal alloantibodies targeted against fetal HPA-1a.^6–8^ FNAIT is considered to be the platelet counterpart of haemolytic disease of the fetus and the newborn (HDFN) because of their similar pathophysiologic fundaments. In this comparison, HPA-1a, that causes 90% of the ICH caused by FNAIT, is regarded to be the equivalent of rhesus D (RhD) of the red blood cell (RBC) in HDFN.^8^ Important differences, however, exist as well. First, whereas RhD is only expressed on RBCs, the HPA-1a epitope expressed on platelets is also present on the membrane of endothelial cells and syncytiotrophoblast cells.^9 10^ Second, whereas RhD is mainly a problem of second or subsequent incompatible pregnancies, more than half of the severe cases of HPA-1a-mediated FNAIT already occur in firstborn children.^4 11^ For decades, the possibility of prevention of FNAIT by population-based screening for HPA-1a is discussed, in analogy to the RhD prophylaxis and erythrocyte immunisation screening.^12–14^

Careful evaluation of the feasibility, benefits, harms and cost-effectiveness of a possible FNAIT screening programme showed that knowledge is missing on different aspects of the disease. First, despite a couple of large prospective cohort studies, no data exist on the natural history of the disease. Most of the large prospective, screening studies performed, were not only observational, but included some kind of intervention, thereby making it impossible to draw any firm conclusion on the natural history of FNAIT.^15–19^ Further, more accurate estimates of incidence and prevalence of the disease in the Dutch population need to be known. One of the most important differences, making it hard to implement a programme similar to the antenatal screening programme for erythrocyte immunisation, is the lack of tools to identify pregnancies at high risk for developing bleeding complications. Detecting HPA-1a negative women and further HPA-1a alloimmunised pregnancies can be done easily. When alloimmunisation is detected in HDFN, several parameters, laboratory as well as clinical, are available to assess disease severity and to predict which cases would benefit from treatment. For example, RBC alloantibody titre and functional assays such as an antibody-dependent cellular cytotoxicity assay can be performed, followed in preselected cases by estimation of fetal anaemia by Doppler-based assessment of flow velocity in the middle cerebral artery of the fetus. In this way, high-risk cases are identified that most likely benefit from fetal blood sampling (FBS), followed by an intrauterine transfusion.^20^ Treating all HPA-alloimmunised pregnancies with IVIg would lead to a considerable and undesirable overtreatment. So, identification of HPA-alloimmunised pregnancies at high risk for disease, like in HDFN, would be preferable as well. FBS to determine fetal platelet count and if necessary administer intrauterine platelet transfusion can be performed in these pregnancies as well. However, in potentially thrombocytopenic fetuses, this is a risky procedure with a high rate of associated complications.^5^ Unfortunately, no non-invasive laboratory or clinical diagnostic tests to select HPA-alloimmunised pregnancies that would benefit from treatment are applicable in a clinical setting.

To obtain information necessary to judge the effectiveness and feasibility of a potential population-based screening, we designed the HPA-screening in pregnancy (HIP) study. With the HIP study, we aim to collect data on the incidence of HPA-1a alloimmunisation and clinically relevant FNAIT in the Netherlands. The study will be completely observational. This way we will be able to conclude on the natural history of FNAIT. Ultimately, by comparing test characteristics of blood samples from pregnancies with and without clinical manifestations of bleeding, we aim to develop one or more diagnostic tools, allowing more effective and personalised management by selecting pregnancies at high risk for bleeding complications that have the highest chance to benefit from antenatal preventive treatment with IVIg. This would not only be desirable in current management of FNAIT but also especially in potential future screening setting.

## Methods and analysis

### Study objectives

The primary objective of this study is to determine incidence of HPA-1a alloimmunisation and the incidence of clinically relevant HPA-1a-induced FNAIT in the Netherlands. Clinically relevant FNAIT will be defined as minor bleeding (haematoma, bruising, petechiae or small visceral bleeding) and severe bleeding (ICH or internal organ haemorrhage) with the presence of an anti-HPA-1a alloantibody. Additionally, as secondary objective, we aim to collect a set of blood samples that can contribute to the development of a risk assessment model to be used as a diagnostic tool enabling the identification of alloimmunised pregnancies that are at high risk of developing bleeding complications.

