### Study outcomes

The main study parameters/primary endpoints are

Incidence of HPA-1a negativity in the RhD-negative or Rhc-negative pregnant population in the Netherlands at 27 weeks of pregnancy.Incidence of HPA-1a alloantibodies in the tested population at 27 weeks of pregnancy.Incidence of clinically relevant HPA-1a-mediated FNAIT; classified as mild or severe FNAITSevere FNAITICH.Internal organ haemorrhage.Mild FNAITNeonatal bleeding signs other than ICH or internal organ haemorrhage: haematoma, bruising, petechiae, purpura, mucosal or visceral bleeding.Thrombocytopenia for which treatment was administered (platelet transfusion or IVIg) or for which clinical observation was performed.

Our secondary study parameters/endpoints are:

Neonatal treatment for thrombocytopenia: platelet transfusion (with random-donor platelets vs compatible platelets), IVIg, RBC transfusion.Neonatal morbidity: small for gestational age, infection, hours/days in hospital (neonatal intensive care unit vs medium care), need for additional treatment, congenital abnormalities, other causes causing increased bleeding tendency.Neonatal laboratory findings: platelet count, haemoglobin, C-reactive protein.

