#### Phase I

After regular screening, authorisation and correspondence of the results for the prenatal screening programme for erythrocyte immunisation, the tubes are made available for the HIP study. For the HIP study, the platelet-containing plasma of the stored blood tubes is serologically typed for HPA-1a, using a sandwich ELISA. In short, 20 µL of plasma containing platelets will automatically be pipetted into microtiter plates that have been coated with a monoclonal antibody CLBthromb/1 (C17) directed against glycoprotein IIIa, at a concentration of 3 µg/mL to capture all platelets from the plasma. Then horseradish peroxidase-conjugated (HRP-conjugated) B2G1, an antibody targeting HPA-1a, will be added and plates will be centrifuged and incubated for 45 min. Finally, after washing of the plates, HRP-substrate solution will be added for 15 min, and after stopping of this reaction, the reactions will be quantified using an ELISA reader (Biochrom Anthos, Cambridge, UK). This HPA-1a ELISA was specifically designed for the HIP study, thus for quick and high-throughput screening. All samples with an ELISA value below a defined optic density are called HPA-1a negative. The HPA-1a typing result is supported with an allelic discrimination PCR assay. Plasma and buffy coat of samples that are typed HPA-1a negative will be stored at −20°C, using only a study number. Additionally, for each HPA-1a negative case, material of one HPA-1a positive control will be stored simultaneously.

Because this first phase comprises serological HPA-1a typing, which is performed with fresh material, and a delay in the arrival of consent forms might exist, this phase is performed with all samples from pregnant women who did not decline participation for the HIP study. All consecutive phases, such as antibody screening, risk-assessment development and clinical data retrieval, are solely performed in case of informed consent for the HIP study.

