Further underestimation might occur due to the fact that we will perform only a single screening for anti-HPA-1a alloantibodies, that is, at 27 weeks gestation. Immunisations that occur later in pregnancy or after delivery will not be detected. Also, immunisations that will result in complications and termination of pregnancy or IUFD before 27 weeks gestation will not be identified. However, in terms of assessing feasibility and cost-effectiveness of population-based screening, a slight underestimation is unquestionably preferred to an overestimation. On the contrary, we use another antibody screening method compared with earlier screening studies, which is possibly more sensitive compared with the monoclonal antibody immobilisation of platelet antigens (MAIPA) technique.^35^ The PAK Lx assay was tested on a series with 100 cases with suspected FNAIT by our research group in 2014. In 26 of these cases, anti-HPA-1a was detected by MAIPA, all cases were detected and one more by PAKLx. Overall, to our knowledge, the HIP study will be a unique study to prospectively and observationally collect data on incidence and natural history of FNAIT by including this large number of pregnant women without performing any kind of intervention. Additionally, it will be the first study to be able to identify a unique and unbiased study group, that is, immunised pregnant women without disease and without intervention. This is the pre-eminent group to be used for the development of a risk-assessment platform in order to select immunised pregnancies that are at high risk to develop bleeding complications and would therefore benefit from antenatal preventive measures, such as IVIg treatment.

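### Mild and total FNAIT count any minor bleed in an antibody-positive pregnancy, so background neonatal bleeding is attributed to HPA-1a and their incidence is biased upward

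*Protocol article*

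**What the plan says.** The Study objectives give the case definition: "Clinically relevant FNAIT will be defined as minor bleeding (haematoma, bruising, petechiae or small visceral bleeding", with severe bleeding listed next to it, and one linking condition, "with the presence of an anti-HPA-1a alloantibody". Study outcomes makes the incidence of clinically relevant FNAIT a primary endpoint, split into mild and severe. Its mild category covers "haematoma, bruising, petechiae, purpura, mucosal or visceral bleeding", with treated or observed thrombocytopenia as a separate route in. Alternative explanations for a bleed appear only in a secondary morbidity item, "other causes causing increased bleeding tendency". The strengths and limitations list says that the investigators "do not obtain cord blood platelet counts or perform routine neonatal cerebral ultrasounds".

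On comparators, the Abstract states: "Clinical data of HPA-1a negative women and an HPA-1a positive control group will be collected after birth". Phase I adds that "for each HPA-1a negative case, material of one HPA-1a positive control will be stored simultaneously". Phase II says that the caregiver who completes the form does not know the woman's HPA-1a status. The one comparison with controls that the article spells out is for ICH, in the Sample size calculation.

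On bias, the Discussion names missed subclinical cases, immunisation after 27 weeks and losses before 27 weeks. It concludes that "a slight underestimation is unquestionably preferred to an overestimation".

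**The concern.** The endpoint is labelled as induced or mediated by HPA-1a, but the operational rule is co-occurrence of a bleeding sign and a maternal antibody. Newborns can have bruises and haematomas for reasons unrelated to the antibody, delivery among them. Under the rule, each of these becomes a case of mild FNAIT whenever the mother is antibody positive.

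No later step in the article removes them. Platelet counts are not routine. The reporting caregiver is blind to HPA-1a status, and under Ethics and dissemination antibody testing takes place long after birth, so nobody at the bedside can judge attribution. What remains is a later match of a bleeding report with an antibody result.

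Two results are at stake. One is the mild and combined incidence, which feeds the judgement on screening and would err in the direction that the authors like less. The other is Phase IV, which contrasts immunised pregnancies with and without clinical manifestations. Background bleeds in the affected group would weaken that contrast, by an amount that cannot be calculated here.

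**Working it through.** **1. Reproduce the plan's figure.** Table 1 has 60 000 women included, 2.1% HPA-1a negative, and antibodies in 10% of those. 60 000 × 0.021 = 1260 and 1260 × 0.10 = 126, both as printed. One control per HPA-1a negative case gives about 1260 controls, if consent and forms are complete.

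**2. ICH, where the article gives a background rate.** The Sample size calculation assumes 4.9 per 10 000 in controls and 3% in immunised cases. Expected background cases: 126 × 0.00049 = 0.06. Expected cases at 3%: 126 × 0.03 = 3.8. The definition does no harm here.

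**3. Minor bleeding, where it gives none.** Let b be the background risk and e the true antibody-related risk; both are assumptions. The observed risk is e + (1 − e)b. The number of background bleeds labelled FNAIT is at most 126 × b, and their share of counted cases is (1 − e)b / [e + (1 − e)b].

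| Assumed b | 126 × b | Share if e = 5% | Share if e = 10% | Share if e = 30% |
|---|---|---|---|---|
| 1% | 1.3 | 16% | 8% | 2% |
| 2% | 2.5 | 28% | 15% | 4% |
| 5% | 6.3 | 49% | 31% | 10% |
| 10% | 12.6 | 66% | 47% | 19% |

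Per 100 000 included pregnancies, the upper bound runs from 1.26 / 60 000 = 2.1 to 12.6 / 60 000 = 21.

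**4. Antigen-negative children.** Under Hardy-Weinberg, 2.1% negativity gives an allele frequency of √0.021 = 0.145. At most 14.5% of the children of HPA-1a negative women are therefore antigen negative, and fewer among women immunised in the current pregnancy. With b = 5% that is at most 126 × 0.145 × 0.05 = 0.9 cases, already inside the 6.3 above.

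**5. What the control comparison recovers, and its price.** Immunised minus control risk is e + (1 − e)b − b = e(1 − b), close to e when b is small. For observed risks of 10% (n = 126) and 5% (n = 1260), the 95% half-width is 1.96 × √(0.10 × 0.90/126 + 0.05 × 0.95/1260) = 0.054. The crude 10% alone has 1.96 × √(0.10 × 0.90/126) = 0.052.

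**The case against.** The best counter-argument is that this is a condensed article. Its Statistical analysis section covers data entry, software and an interim look, and names no estimator for any endpoint. The analysis plan may well compare mild bleeding with controls, and one blinded control per HPA-1a negative case is just the set-up that this needs. A reader might infer that the controls will serve only the ICH calculation. The article does not support that: other use is unstated, not ruled out. What the article does fix is the case definition, and that counts background bleeds as FNAIT whatever comparison is added later.

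Second, the size is assumed throughout. The background share in the table runs from 2% to 66%. The article relies on clinical judgement of bleeding tendency after birth, so caregivers may record less than every bruise, and the figure listing the form's items is not shown. A reader might infer that the reported incidence would be about double the true one. That needs a pairing such as e = 5% and b = 5%, which nothing in the article supports or excludes.

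Third, the Discussion puts ICH at the centre of any screening benefit, and ICH is unaffected. This stands, and it confines the point to mild and combined FNAIT. Missed subclinical cases and late immunisations also pull downward, so the net direction for total incidence is not established. Nor do the authors call overestimation unacceptable; they state a preference.

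Fourth, incidence of bleeding with antibody present is a legitimate descriptive quantity. That also stands, and it is a reason to keep the crude proportion under an accurate name.

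**Conclusion.** The point holds for mild FNAIT and for the combined mild-plus-severe incidence, which together make up most of a primary endpoint's definition. The stated rule attributes background bleeding to HPA-1a, and this component of error is upward. The Discussion does not mention it. ICH incidence is not materially affected.

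The size is unknown from the documents: about 1 to 13 of 126 immunised pregnancies if the background rate lies between 1% and 10%. That rests on the assumed rate and on Table 1's expected numbers being met. The missing fetal HPA-1a type adds little of its own. A change is worth making because the labels claim causation, the definition does not establish it, and the comparator that would is already in hand.

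**What to change.** - Keep the crude antibody-plus-bleeding proportion, but label it bleeding in immunised pregnancies.
- Beside it, report the same signs, recorded on the same form, in the HPA-1a positive controls. Use the non-immunised HPA-1a negative women as a second comparator (about 1260 − 126 = 1134 expected).
- Report the risk difference against the HPA-1a positive controls, with its 95% confidence interval, as the HPA-1a-attributable incidence of mild and of total FNAIT.
- As a sensitivity analysis, exclude infants with another recorded cause of bleeding tendency, in the immunised and comparison groups alike.
- Add a sentence to the Discussion naming background bleeding as a source of overestimation for mild FNAIT.

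The cost is a few lines of analysis text and no new data. The statistical price is the slightly wider interval shown above, 5.4 against 5.2 points either side when the risks are 10% and 5%.

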### Study design

The HIP study is a nationwide prospective and observational cohort study, conducted in all settings of obstetric care in the Netherlands, for a period of 2.5 years.

### Patient and public involvement

In 2008, the Ministry of Health, Welfare and Sport (in Dutch: Ministerie van VWS) gave instructions to investigate preventive interventions for 27 significant health problems that could be cost-effective. As a result, the National Institute for Public Health and the Environment (in Dutch: RIVM) published a report stating that antenatal screening for FNAIT would be cost-saving, but they advised that more knowledge on natural history of the disease and treatment of detected cases should be obtained to support possible implementation of screening.^21^ Also, the RIVM was involved in the design of the study. There was no further involvement of patients or public in the recruitment or the conduct of the study.

### Study population

For logistic purposes, RhD-negative or rhesus c (Rhc)-negative pregnant women were selected for enrolment in the HIP study. As part of the Dutch prenatal screening programme for infectious disease and erythrocyte immunisation (in Dutch: PSIE), these women are offered a free of charge red cell antibody screening and/or fetal RhD typing at 27 weeks gestation. For this, 9 mL EDTA anticoagulated blood is drawn by their midwife or at certified, local laboratories all over the Netherlands (n=±90) and transported to the Sanquin laboratory in Amsterdam by regular surface mail or private courier service. The programme has a voluntary participation grade of 99%.^22 23^ With approval of the RIVM, that organises this population screening programme, left-over material can be used for the HIP study for HPA-1a typing and stored for further antibody testing after informed consent.

#### Inclusion criteria

Prior to enrolment, participants have to fulfil these following criteria:

Pregnant women participating in the currently implemented prenatal screening programme for erythrocyte immunisation and who are typed RhD or Rhc negative.Ability to make an informed decision on participating in the population screening programme as well as in the HIP study.

